### Objectives

The current study protocol aims to (1) investigate the influence of opposing EA treatment on the brain activities of patients after unilateral TKA compared with that of sham opposing EA treatment and (2) analyze the possible correlations between the changes in cerebral activity and the improvement of clinical variables in each group, exploring how opposing EA modulates brain function to manage acute pain after TKA.

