#### Scheme of standard analgesic use

Within 48 h after TKA, participants will use a patient-controlled analgesia pump. Fentanyl (Yichang Renfu Pharmaceutical Co., Ltd., Yichang, China) will be used as an analgesic drug at a continuous infusion rate of 0.25 μg/kg/h, a bolus dose of 0.15 μg/kg, and a 10-min lockout time. In addition, all participants will begin oral administration of celecoxib capsules (Pfizer Pharmaceutical Co., Ltd., New York, USA), at a dosage of 200 mg once daily, 72 h after operation.

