### Statistical analysis

Based on the intention-to-treat principle, a full analysis set and per-protocol sets will be used for the primary analysis. Sensitivity analysis will be performed to determine the impact of incomplete records on the results. Missing data will not be imputed. For the clinical data, statistical analyses will be performed using the statistical package IBM SPSS Statistics V21 (IBM Corp., Armonk, NY, USA). Complete follow-up assessments of the participants will be performed using the per-protocol and intention-to-treat populations. The statistical analysis will include four aspects. First, for the measured data with normal and non-normal distributions, the mean ± SD and median will be used to describe the concentration trend and dispersion degree, respectively. Two independent sample *t*-tests and Mann-Whitney *U* tests will be used to compare the differences between groups. Second, the quadruple chi-squared test will be used to evaluate the sex composition ratio (which is a classified variable). Third, the Mann-Whitney *U* test will be used to compare the differences between the groups in the ranked data. Finally, a generalized linear mixed model will be used to compare the repeated measurement data. The statistical significance will be set to two-sided *p* < 0.05.

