The fMRI scan data will be preprocessed and analyzed using SPM12 software (http://www.fil.ion.ucl.ac.uk/spm/) performed on MATLAB 2015b (MathWorks, Inc., Natick, MA, USA). The main preprocessing steps are as follows: (1) remove the functional image data of the first 10 time points while waiting for the imaging gradient to reach a stable state; (2) carry out time correction, remove the time difference between different layers by correction, and then perform head correction; (3) match the functional image to the corresponding anatomical image and convert it to a standard Montreal Neurological Institute space—the resampling size of the image data pixels is 3 × 3 × 3 mm^3^; (4) use the linear regression method to remove the related variables, including the average signal of the cerebrospinal fluid and 12 cephalic parameters; and (5) process the data by removing high-frequency noise and low-frequency drift. The data are mainly processed by linear drift and band-pass filtering (0.01–0.08 Hz). After data preprocessing, the amplitude of low-frequency fluctuation, regional homogeneity, and functional connectivity will be used to investigate the cerebral responses of the different study groups. A two-sample *t*-test will be used to evaluate intra- and inter-group differences to analyze possible brain responses, and a correlation analysis will be conducted to investigate the changes in fMRI image data and the corresponding clinical data in each group.

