FMRI is a large-scale neural network technique. As the main type of fMRI, blood oxygen level-dependent fMRI measures neuronal activity using the ratio of oxyhemoglobin to deoxyhemoglobin as a contrast mechanism [61]. With the advantages of high imaging speed, non-radiation, and non-invasiveness [62, 63], it has become a commonly used neuroimaging technique in the research of the central mechanism of acupuncture [64, 65]. Relative to task-related fMRI, rs-fMRI has the advantage of providing more comprehensive information on the functional architecture of the brain [61]. Using rs-fMRI, some investigators have found that acupuncture can exert an analgesic effect by directly regulating the anterior cingulate gyrus. Their results also suggested that acupuncture on the opposite side and ipsilateral side can induce different brain mechanistic changes [33].

In this trial, we will adopt direct quality control measures to reduce bias and improve the reliability of the results. In addition to establishing strict inclusion and exclusion criteria at the stage of participant recruitment, demographic characteristics such as age and handedness will also be applied as inclusion criteria. The mode of operation and the type and dose of perioperative medication will be regulated as much as possible, and factors that may affect brain activity, including coffee drinking or alcohol and drug abuse, will also be considered. The acupuncturist will receive standardized training before the trial and carry out all treatments in accordance with standard operating procedures. During acupuncture, unnecessary communication between the acupuncturist and the patient will be prohibited. The personnel responsible for the analysis will be trained and blinded to the test group.

In summary, the purpose of this trial is to study the main mechanism of opposing EA in the management of acute pain after TKA by analyzing the correlation between changes in brain activity and clinical variables. We hope that our findings can provide a visual reference for the clinical application of opposing needling after TKA.

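### Brain-clinical correlations are planned within each arm and used to infer the EA mechanism, but no comparison of them between arms is named

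*Protocol article*

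**What the plan says.** The second aim in the Objectives section is to "analyze the possible correlations between the changes in cerebral activity and the improvement of clinical variables in each group", in order to explore how EA acts on brain function. The fMRI paragraph of Statistical analysis carries this through: "a correlation analysis will be conducted to investigate the changes in fMRI image data and the corresponding clinical data in each group". On the brain side, "the amplitude of low-frequency fluctuation, regional homogeneity, and functional connectivity will be used". The closing summary of the Discussion says that the main mechanism of EA will be studied "by analyzing the correlation between changes in brain activity and clinical variables".

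The one inter-group fMRI comparison named is a two-sample t-test. The plan says that this "test will be used to evaluate intra- and inter-group differences to analyze possible brain responses". It applies to the brain measures, not to their relation with the clinical measures.

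The significance threshold ("The statistical significance will be set to two-sided" p < 0.05) closes the clinical-data paragraph. The protocol gives no expected correlation and no power for the correlation analysis.

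**The concern.** Randomisation supports comparisons between arms. A correlation inside one arm is not such a comparison. Per MRI data acquisition, the two scans bracket the treatment days. Over that time every patient is recovering from surgery and doing daily physiotherapy. Under Scheme of standard analgesic use, "all participants will begin oral administration of celecoxib capsules" at 72 h after the operation, the time at which EA or sham also begins. Patients who recover faster, or respond better to the shared treatment, may show both a larger brain change and a larger pain change, whichever arm they are in.

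The sham arm is there to separate these explanations from EA, but separate per-arm correlations leave it unused for this purpose. The natural way to read two such results is to note which arm reached significance. That contrast does not test whether the relation differs by arm, and its error rate is set by the power of each correlation, not by any difference between arms.

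**Working it through.** **Inputs from the protocol (Sample size).** 40 per group planned; at least 20 per group required; 20% drop-out, so 40 × 0.80 = 32 per group before losses to head movement, which are not quantified. The checks use n = 20, 32 and 40. The plan has no figure of its own for this analysis to reproduce.

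**Assumptions.** The true correlations (a range is shown), bivariate normal data, independent arms, and two-sided 0.05 applied to the correlations.

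**Step 1: power p of one within-arm correlation.** By Fisher's z with standard error 1/√(n − 3), p ≈ Φ(atanh(r)·√(n − 3) − 1.96), plus a small opposite-tail term. For r = 0.4, atanh(r) = 0.424.
- n = 32: 0.424 × √29 = 2.28, so p = 0.626.
- n = 20: 0.424 × √17 = 1.75, so p = 0.416.

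**Step 2: chance of a discordant pattern when both arms have the same true r.** Significant in EA only: p(1 − p), which cannot exceed 0.25. Significant in exactly one arm, either way: 2p(1 − p), which cannot exceed 0.50.
- n = 32, r = 0.4: 0.626 × 0.374 = 0.234; either way 0.468.
- n = 20, r = 0.4: 0.416 × 0.584 = 0.243; either way 0.486.
- r = 0: 0.05 × 0.95 = 0.0475; either way 0.095.

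| Common true r | EA only, n = 20 | n = 32 | n = 40 |
|---|---|---|---|
| 0 | 4.8% | 4.8% | 4.8% |
| 0.2 | 11.5% | 15.6% | 17.9% |
| 0.4 | 24.3% | 23.4% | 19.6% |
| 0.6 | 15.1% | 3.7% | 1.2% |

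The 25% ceiling is reached where each correlation has about 50% power: r = 0.44, 0.35 and 0.31 at n = 20, 32 and 40. Simulation with the t-test of r (40,000 pairs of arms per setting) agrees within about 2.5 percentage points.

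**Step 3: a direct test.** Compare atanh(r) between arms with standard error √(2/(n − 3)). In simulation its two-sided error was 4.9–5.1% at all three sample sizes and every common r from 0 to 0.7. By symmetry about 2.5% falls in the EA-favouring direction.

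**Step 4: power of the direct test.** For an assumed r = 0.5 versus 0, the difference in z is 0.549.
- n = 20: 0.549/√(2/17) = 1.60, power 36%.
- n = 32: 0.549/√(2/29) = 2.09, power 55%.
- n = 40: 0.549/√(2/37) = 2.36, power 66%.

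80% power would need 56 per group. For r = 0.5 versus 0.2 it would need 134. These figures are for comparing correlations; a slope interaction behaves similarly when the spread of both measures is alike in the two arms.

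**The case against.** The strongest reply is that the protocol states no rule that significance in EA alone proves a mechanism. It promises correlations in each group and nothing more. The Abstract and Objectives use tentative wording (possible relationships, exploring). Objective 1 is a proper randomised comparison of brain activity, so the mechanism question does not rest on the correlations alone. All of this stands. What remains is that the by-group form is written twice, the Discussion's summary ties it to the EA mechanism, and nothing named compares the relation between arms.

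The shared drugs are also balanced by design, and a constant exposure does not itself create correlation between patients. That is correct. Only variation in recovery or response does so, and it can occur in both arms.

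An interaction, moreover, tests whether the relation differs by arm. If EA relieves pain through a pathway that both arms share, the slopes are equal and the interaction is null although the mechanism is real. This stands too and limits what the fix can claim.

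Two stronger readings are tempting:
- A reader might infer that the EA-only pattern arises about half the time when the arms do not differ. Half is the ceiling for either direction; for EA only the ceiling is one in four, and with strong correlations the rate is far lower.
- A reader might multiply three metrics by four clinical measures by two arms and quote 1 − 0.95^24 = 71% for at least one significant result. The protocol gives no count of correlations, the measures come from the same patients and scans and so are not independent, and the 0.05 threshold stands in the clinical-data paragraph. Image thresholds and multiplicity control may properly sit in a fuller plan.

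**Conclusion.** The point holds as a limit on inference. As written, the correlation analysis cannot attribute a brain-clinical relation to EA rather than to what both arms share. If the two arms' significance were contrasted, equal and moderate true correlations would yield an EA-only pattern up to 25% of the time, against 2.5% for a direct test in that direction. With both correlations zero the rate is about 5%, counting correlations of either sign. These are rates for a single correlation and depend on assumed true values that the protocol does not give. That investigators would read the pattern as an EA mechanism is a reasonable inference from the Objectives and Discussion, not a stated rule. An unseen analysis plan could add the between-arm test, but the text shown fixes the by-group form.

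**What to change.** Analyse both arms in one model: clinical change, adjusted for its baseline value, on group, brain change and group × brain change. Report the interaction and the common slope, each with a confidence interval. Keep the per-arm correlations as descriptive results.

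State three things beside it: the interaction tests whether the relation differs by arm; a null interaction does not rule out a pathway shared by both arms; and the analysis is exploratory, because power is low at the available sample sizes.

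The cost is a change of analysis wording and a little more analysis, with no new patients, scans or measurements. The downside is fewer significant correlations to report.

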## Discussion

This is a randomized, sham-controlled fMRI study to explore how opposing needling acupuncture relieves postoperative knee pain by regulating brain function after TKA in patients with KOA.

In recent years, pain management has been widely used in the perioperative period as a core concept of accelerated rehabilitation surgery [54, 55]. Optimal postoperative pain management can effectively prevent and reduce adverse reactions and stress reactions. For this, multimodal analgesia should be adopted, and the development of multidisciplinary analgesia methods should be promoted [56, 57]. Acupuncture, a traditional Chinese medicine, has achieved good results in promoting analgesia after TKA [58, 59].

According to the traditional acupuncture meridian theory and the principle of acupoint adjacent treatment, SP9 and GB34 near the knee joint have been selected as the acupoints of the foot Taiyin spleen meridian and foot Shaoyang gallbladder meridian, respectively, for use in this study. In addition, we select the ST36 and ST32 acupoints of the stomach meridian of foot Yangming. In the theory of traditional Chinese medicine, spleen *qi* is the biochemical source of human *qi* and blood; therefore, these two acupoints have been selected to promote the operation of human *qi* and blood and to improve the state of *qi* and blood stasis caused by injury to the knee joint after surgery.

Opposing needling refers to acupuncture to healthy lower limbs. Increasing evidence from clinical and experimental studies shows that opposing needling has a protective effect and promotes functional rehabilitation, but its mechanism remains to be elucidated [60]. In patients who have undergone orthopedic lower limb surgery, acupuncture on the unaffected limb is more acceptable, and patient compliance is higher. Furthermore, this acupuncture method avoids direct invasive intervention in the surgical area and reduces the risk of postoperative infection to a certain extent.

FMRI is a large-scale neural network technique. As the main type of fMRI, blood oxygen level-dependent fMRI measures neuronal activity using the ratio of oxyhemoglobin to deoxyhemoglobin as a contrast mechanism [61]. With the advantages of high imaging speed, non-radiation, and non-invasiveness [62, 63], it has become a commonly used neuroimaging technique in the research of the central mechanism of acupuncture [64, 65]. Relative to task-related fMRI, rs-fMRI has the advantage of providing more comprehensive information on the functional architecture of the brain [61]. Using rs-fMRI, some investigators have found that acupuncture can exert an analgesic effect by directly regulating the anterior cingulate gyrus. Their results also suggested that acupuncture on the opposite side and ipsilateral side can induce different brain mechanistic changes [33].

In this trial, we will adopt direct quality control measures to reduce bias and improve the reliability of the results. In addition to establishing strict inclusion and exclusion criteria at the stage of participant recruitment, demographic characteristics such as age and handedness will also be applied as inclusion criteria. The mode of operation and the type and dose of perioperative medication will be regulated as much as possible, and factors that may affect brain activity, including coffee drinking or alcohol and drug abuse, will also be considered. The acupuncturist will receive standardized training before the trial and carry out all treatments in accordance with standard operating procedures. During acupuncture, unnecessary communication between the acupuncturist and the patient will be prohibited. The personnel responsible for the analysis will be trained and blinded to the test group.

In summary, the purpose of this trial is to study the main mechanism of opposing EA in the management of acute pain after TKA by analyzing the correlation between changes in brain activity and clinical variables. We hope that our findings can provide a visual reference for the clinical application of opposing needling after TKA.

## Trial status

The trial is currently in the process of recruiting participants. Recruitment for the trial began on March 10, 2021, and is expected to be completed on March 31, 2022.

## Data Availability

The datasets and the informed consent forms can be obtained from the corresponding author upon reasonable request.

## Abbreviations

TKA: Total knee arthroplasty
KOA: Knee osteoarthritis
EA: Electroacupuncture
MRI: Magnetic resonance imaging
fMRI: Functional magnetic resonance imaging
rs-fMRI: Resting-state functional magnetic resonance imaging
PPTs: Pressure pain thresholds
VAS: Visual analogue scale
4MWT: 4-m walking test
sEMG: Surface electromyography
SAS: Self-rating anxiety scale
SDS: Self-rating depression scale
